## Abstract

**Introduction:**

Trigeminal neuralgia (TN) is extremely vulnerable to inducing anxiety disorders in TN patients owing to the severe intensity of pain and recurrent episodes. The efficacy of the routine management of TN with anxiety disorders is still unsatisfactory. Acupuncture has been widely utilized in the treatment of TN for many years; however, the effectiveness of Electroacupuncture (EA) for TN with anxiety disorders remains uncertain. Therefore, this randomized, controlled, single-blinded trial was designed to investigate the efficacy and safety of EA for TN with anxiety disorders.

**Methods:**

This single-center, prospective, randomized controlled trial will recruit 60 TN patients with anxiety. All patients will be randomly assigned to the EA or sham EA group in a 1:1 ratio via a computerized central randomization system. The total trial duration is 18 weeks, including a 2-week baseline phase, a 4-week treatment phase, and a 12-week follow-up phase. Participants who meet the inclusion criteria will receive active EA or sham EA treatment for 60 min, three times a week, for 4 weeks.

**Planned Outcomes:**

The primary outcome is the change of Beck Anxiety Inventory score and Visual Analog Scale score from baseline, while the BPI-Facial scores will be regarded as the secondary outcomes. All adverse effects will also be assessed during the study period. Outcome measures will be assessed at pre-intervention, post-intervention (week 4), and at the end of follow-up (week 16).

**Trial Registration:**

Chinese Clinical Trial Registry: ChiCTR2300079048. This study was registered on December 25, 2023.

## Introduction

Trigeminal neuralgia (TN) is a facial pain disorder characterized by unilateral, transient, and recurrent episodes, and is mainly confined to one or more branches of the trigeminal nerve distribution (1, 2). More recently, there has been a gradual increase in the incidence of TN, with an annual rate of approximately 12.6/100, 000 person-years (3), and higher in females (4). Due to the deep intensity of pain and recurrent

attacks, patients with TN are more susceptible to anxiety (5), which seriously affects their quality of life, and has even been historically referred to as a ‘suicidal disease' (6, 7). Notably, anxiety can further exacerbate the degree of pain, thereby affecting the efficacy of the treatments (8). However, the psychological consequences of TN, especially anxiety, have received remarkably less attention.

Pharmacotherapy and psychotherapy are the main therapies for anxiety and have a significant contribution to the improvement of negative emotions, i.e., anxiety disorder (7, 9, 10). Oral selective serotonin reuptake inhibitors are the first-line pharmacologic treatment for anxiety disorders due to their robust efficacy, although other medications may also be efficacious (11–13). Nevertheless, various adverse effects (AEs) are associated, such as headaches, addiction and suicidality (14, 15). Currently, various psychological treatments for anxiety disorders, i.e., mindfulness-based intervention, acceptance and commitment therapy, psychodynamic therapy, emotion-focused therapy, and dialectical behavioral therapy have been tried (16), while some controversies about the efficacy of these interventions remain (17). Moreover, psychotherapy was limited by the scarcity of psychotherapists and the enormous socio-economic costs (18). Hence, there is an urgent demand to find a superior, cost-effective, and secure alternative treatment that reduces the intensity of pain in patients with TN, while ameliorating anxieties.

Acupuncture, a common treatment in Traditional Chinese Medicine, has been widely used for many years in the management of TN, particularly in patients who are medically refractory (19, 20). Meta-analysis demonstrated that electroacupuncture (EA) may be more effective at reducing pain intensity than carbamazepine (CBZ) or other common therapies (21, 22). Recently, [name] conducted a randomized controlled trial of EA combined with CBZ in 120 TN patients, further confirming the effectiveness of EA. Additionally, the greater benefit of EA combined with low-dose CBZ (300 mg/d) was also revealed in this study, providing a tangible alternative therapeutic choice for TN who cannot tolerate high-dose CBZ (4). Both acupuncture and EA are effective in treating anxiety on their own or as adjuncts to pharmacological therapy (23). Meanwhile, acupuncture can effectively alleviate the anxiety disorders associated with the symptoms, reduce the anxiety score, and improve the prognosis of the disease (24–26), while the quality of studies examining extremely variable (27). Notably, there is currently no effective therapy for TN accompanied by anxiety, and the effectiveness of EA in the treatment of TN with anxiety remains uncertain.

To date, high-quality evidence regarding the therapeutic effect of EA for TN accompanied by anxiety disorders is still lacking (28). Hence, this RCT aims to investigate the efficacy and safety of EA for TN accompanied by anxiety disorders.

## Methods

### Study design

This single-blind RCT will be conducted at *the Acupuncture Department of the Third Affiliated Hospital of Zhejiang Chinese Medical University*. 60 eligible participants diagnosed with TN comorbid with anxiety will be randomized into two groups: EA and sham EA. The total trial duration is 18 weeks, including a 2-week baseline phase, 4-week treatment phase, and 12-week follow-up phase (Figure 1), and the schedule of enrolment, treatments, and assessments is demonstrated in Table 1. This trial protocol follows the SPIRIT 2025 Statement: Updated Guideline for Protocols of Randomized Trials (29), and the modified CONSORT flow diagram is shown in Figure 2.

**Figure 1 F1:**
[figure not shown]
Study design. EA, Electroacupuncture. Rescue medication will be allowed throughout the trial (baseline, treatment phase, follow-up phase), with a maximum daily dosage of 600 mg. The timing and dosage of all rescue medications will be recorded.

**Table 1 T1:** Schedule of enrolment, treatments, and assessments.

Study period	Screening	Baseline	Treatment period	Follow-up period
		Week−2-0	Week 4	Week 16
Eligibility screening	^ ***** ^			
Demographic data	^ ***** ^			
Case data	^ ***** ^			
History of TN	^ ***** ^			
History of treatment	^ ***** ^			
Inclusion criteria	^ ***** ^			
Exclusion criteria	^ ***** ^			
Informed consent	^ ***** ^			
Treatment condition			^ ***** ^	
Outcome assessment				
(1) BAI		^ ***** ^	^ ***** ^	^ ***** ^
(2) VAS		^ ***** ^	^ ***** ^	^ ***** ^
(3) BPI-facial		^ ***** ^	^ ***** ^	^ ***** ^
Safety assessment			^ ***** ^	^ ***** ^
Recurrence				^ ***** ^

^*^Required; BAI, Beck Anxiety Inventory; VAS, Visual Analog Scale; BPI-Facial, Brief Pain Inventory-Facial Scale.

**Figure 2 F2:**
[figure not shown]
Flowchart of the study process. Bal, Beck Anxiety Inventory; VAS, Visual Analog Scale; BPI Facial, Brief Pain Inventory-Facial Scale.

### Ethical considerations and trial registration

This trial will be conducted in accordance with the Declaration of Helsinki, and ethical approval was obtained from the Clinical Trial Ethics Committee of *the Third Affiliated Hospital of Zhejiang Chinese Medical University* (Approval No.: ZSLL-KY-2023-039-01). All patients need to sign informed consent forms before enrolling in this study. Additionally, the trial has been prospectively registered on the *Chinese Clinical Trials Registry*, with registration number ChiCTR2300079048.

### Eligibility criteria

#### Inclusion criteria

(1) diagnosed with TN meet IHCD-3 criteria (30); (2) shooting pain, electric shock pain, or stabbing pain occurring in one or more branches of the trigeminal nerve; (3) Visual Analog Scale (VAS) score ≥4 at baseline, more than three episodes per day, and occurring on at least 4 days per week; (4) male or female participants, age from 18 to 80 years old; (5) Beck Anxiety Inventory (BAI) score ≥16; (6) patients who are conscious, communicate normally, and willing to sign a written informed consent form.

#### Exclusion criteria

Participants will be excluded for the following conditions: (1) patients with secondary TN (e.g. intracranial tumors, multiple sclerosis, etc.); (2) head injury, epilepsy, or other related neurological disorders; (3) cognitive dysfunction, aphasia, or mental disorders, and pain-impaired psychiatric disorders; (4) patients who are pregnant or breastfeeding; (5) not suitable for EA, such as being fitted with a pacemaker; (6) patients with psychogenic pain disorders. Notably, included patients received free treatment to improve compliance.

The specific inclusion/exclusion criteria of eligible TN patients are listed in Table 2.

**Table 2 T2:** Inclusion criteria and exclusion criteria of TN patients.

Inclusion criteria	Exclusion criteria
(1) Diagnosed with TN meet IHCD-3 criteria (2018)	(1) Patients with secondary TN (e.g., intracranial tumors, multiple sclerosis, etc.)
(2) Shooting pain, electric shock pain, or stabbing pain occurring in one or more branches of the trigeminal nerve	(2) Head injury, epilepsy, or other related neurological disorders
(3) Visual analog scale score ≥4 at baseline, more than three episodes per day, and occurring on at least 4 days per week	(3) Cognitive dysfunction, aphasia, or mental disorders, and pain-impaired psychiatric disorders (4) Patients who are pregnant or breastfeeding
(4) Male or female participants, age from 18 to 80 years old	(5) Not suitable for EA, such as being fitted with a pacemaker
(5) Beck Anxiety Inventory score ≥16	(6) Patients with psychogenic pain disorders
(6) Patients who are conscious, communicate normally, and willing to sign a written informed consent form	

TN, Trigeminal neuralgia; IHCD, International Classification of Headache Disorders; EA, Electroacupuncture.

### Sample size

Sample size estimation was performed by the “*Powerandsamplesize.com*” online website (31). This study is the first to explore the therapeutic effect of EA for TN with anxiety. Based on our pilot data with emotion scores between groups [EA group: 3.9 (1.2); control group: 1.2 (0.8)] by using an independent two-sample *t-*test design, a minimum of 25 participants per group will be required (two-sided α = 0.05, power = 0.8). To account for a 20% dropout rate, the final sample size will be set to 30 per group (total *N* = 60). This ensures adequate power even with potential attrition.

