### Outcome assessment

#### Primary outcomes

This study adopted dual primary endpoints: changes in BAI score and VAS score from baseline to week 4 post-treatment and week 16 follow-up phase, to fully assess the proposed “dual regulatory effect” of EA in TN patients with anxiety.

The BAI is a widely used anxiety scale for psychological assessment of patients and self-assessment in the general population. It was created by the team of American scholar Aaron T. Beck in 1988, with a total of 21 self-report questions (34). Notably, the scale is primarily designed to measure the degree of anxiety and to evaluate the therapeutic effects of anxiety treatment. The BAI adopted the 4-point Likert scale, ranging from 0 to 3 points for each question, based on the following criteria: ‘0′ means not at all; ‘1′ means mildly, with little annoyance; ‘2′ means moderately, feeling uncomfortable but tolerable; ‘3′ means severely, unbearable. The total score is the sum of all questions, ranging from 0 to 63 points, with a higher total score indicating a greater degree of anxiety. Generally, a participant with a total score between 0 to 7 points is considered to have basically no anxiety symptoms, while 8 to 15 points means mild anxiety, 16 to 25 points is moderate anxiety, and above 26 by severe anxiety.

Pain intensity will be evaluated using a 10-cm VAS anchored by ‘0′ (no pain) on the left and ‘10′ (worst pain imaginable) on the right. Participants will be asked to mark the point on the line that best represents their current pain intensity. The distance in centimeters from the ‘0′ end to the mark will be measured and recorded as the pain score. The *International Association for the Study of Pain (IASP)* recommends using the VAS score to assess pain intensity in patients with neuropathic pain, and to validate pain intensity relief with a particular therapy in a clinical trial (Grade A) (35).

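### The pilot figures given for the sample size need about 4 patients per group, not 25, and the score they describe is not identified with either primary endpoint

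*Protocol article*

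**What the plan says.** The Sample size section of the protocol article gives all the inputs of a conventional calculation. The effect is taken from a pilot: "Based on our pilot data with emotion scores between groups [EA group: 3.9 (1.2); control group: 1.2 (0.8". The test is an independent two-sample t-test, and the result is that "a minimum of 25 participants per group will be required (two-sided α = 0.05, power = 0.8". The number is then raised: "To account for a 20% dropout rate, the final sample size will be set to 30 per group", 60 in total, and the section closes by asserting that power is adequate even with attrition. Allocation is 1:1 (Randomization and blinding).

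The Primary outcomes section names different quantities: "This study adopted dual primary endpoints: changes in BAI score and VAS score from baseline to week 4 post-treatment and week 16 follow-up phase". BAI runs from 0 to 63 and VAS from 0 to 10 cm. Neither section gives an expected difference or a standard deviation for change in BAI or change in VAS. The term *emotion scores* appears only in the Sample size section, without definition.

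**The concern.** There are two separate problems. First, a mean difference of 2.7 against standard deviations of 1.2 and 0.8 is a very large effect, and a t-test needs only a handful of patients to detect it. A requirement of 25 per group does not look like the product of those inputs.

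Second, the score used for planning is not identified. It could be a level or a change, on any instrument, at any time. Without that link, the 80% cannot be carried over to BAI or VAS, which are the endpoints the trial will be judged on.

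At stake is the only stated justification for the number of patients, and with it the claim of adequate power.

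**Working it through.** **Inputs** (Sample size section): means 3.9 and 1.2; parenthesised values 1.2 and 0.8; two-sided α 0.05; power 0.80. Allocation is 1:1. The parentheses are not labelled there. I read them as SDs, as in the mean (SD) convention of the Statistical methods section.

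**Attempt to reproduce 25**

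- Difference: 3.9 − 1.2 = 2.7.
- Pooled SD: √((1.2² + 0.8²)/2) = √1.04 = 1.02.
- Standardised difference: d = 2.7/1.02 = 2.65.
- Normal approximation: n = 2(z₀.₉₇₅ + z₀.₈₀)²/d² = 2 × 7.849/2.65² = 2.24, so 3 per group.
- Exact (noncentral t) power: 68.3% at 3 per group and 87.4% at 4. The requirement is 4 per group.
- Simulated Welch test, with the two SDs kept unequal: 82.3% at 4 per group.
- Power at 25 per group on the same inputs: above 99.9%.

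**Variants**

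| Variant | n per group |
|---|---|
| Pooled SD 1.02 | 3 (normal), 4 (exact) |
| SD 1.2 in both arms (d = 2.25) | 4 (normal), 5 (exact; 75.5% at 4, 87.5% at 5) |
| Pooled SD, α split to 0.025 or 0.0125 | 5 (exact) |
| The two SDs added, 2.0 (d = 1.35) | 9 (normal), 10 (exact) |
| SD 2.0 and power raised to 95% | 15 (normal) |

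The last two rows are deliberately extreme, and even they do not reach 25.

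**Working back from 25.** With 25 per group, two-sided 0.05 and 80% power, the detectable standardised difference is 0.81 by the exact t-test (0.79 by normal approximation). This would need an SD of 2.7/0.81, about 3.3, for the stated difference, or a difference of 0.81 × 1.02, about 0.82, for the stated pooled SD. The article gives neither. The normal approximation for d = 0.8 is 2 × 7.849/0.64 = 24.5, rounded up to 25. That is a numerical match and does not establish where 25 came from.

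**Dropout step.** 30 is 25 × 1.2. Losing 20% of 30 leaves 30 × 0.8 = 24, one below the stated minimum; 25/0.8 = 31.25 would round up to 32. With 24 per group the detectable standardised difference is 0.83.

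**What N delivers.** The article gives no effect size for BAI or VAS, so I assumed a range, for one endpoint at one time point with 24 per group:

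| Assumed d | Power, two-sided 0.05 |
|---|---|
| 0.5 | 40% |
| 0.6 | 53% |
| 0.8 | 77% |
| 1.0 | 92% |

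At d = 0.81 and 25 per group, power falls from 80% to about 71% if α is split to 0.025 and to about 61% at 0.0125. If both endpoints must succeed and each alone has 80% power, joint power is below 80% unless the two are perfectly correlated.

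**The case against.** The strongest reply is that the emotion score may simply be change in BAI. BAI is the only emotional scale in the trial, the primary endpoints are changes, and 3.9 against 1.2 could be mean reductions, with the larger one in the EA group. That is possible, and it limits what can be claimed: the score is unidentified, not shown to be something other than BAI change. For the same reason the higher EA value is no error of direction. The values can hardly be baseline BAI levels, since entry requires at least 16. But reading them as change in BAI still leaves 25 unexplained and says nothing about VAS.

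Other readings can be made to fit. If the parentheses were standard errors from a pilot of about 11 per arm, the SD would be 1.02 × √11 = 3.38 and n about 25 to 26. A superiority margin of about 1.9 would also bring n close to 25. The article states neither a pilot size nor a margin, and its own convention is mean (SD), so neither reading rescues the figure.

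A reader might infer that the trial is too small, or that a null result would be uninterpretable. Neither follows. On the stated inputs 25 per group is far more than enough, and a null result can be read from its confidence interval. Nor can one infer the opposite, that no further patients are needed: without a difference and SD for BAI and VAS, the adequacy of N is open in both directions.

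**Conclusion.** The concern holds in this form: the stated inputs call for about 4 per group (3 to 5 across reasonable variants), not 25, and they are not tied to either primary endpoint. The 80% power and the claim of adequate power are therefore unsupported for change in BAI and change in VAS, at week 4 and at week 16. The arithmetic rests on reading the parentheses as SDs and on the t-test, α and power that the article names. Because the article prints inputs and result together and they disagree, this is a wrong statement and not detail left to a fuller document.

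**What to change.** Correct the Sample size paragraph in one of two ways:

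1. Name the endpoint, time point, difference and SD that produced 25, so that the figure can be reproduced.
2. Delete the emotion-score derivation and state what the fixed N delivers: per single comparison at two-sided 0.05, 80% power for a standardised difference of 0.81 with 25 per group and 0.83 with 24.

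In either case:

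- Express the detectable difference in BAI points and in VAS cm, using a sourced SD, for each primary endpoint at both week 4 and week 16.
- Say that power is lower if α is split or if both endpoints must succeed, with the figures above.
- Remove the claim of adequate power unless it is shown for BAI and VAS.

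The cost is one rewritten paragraph and the work of finding a defensible SD for each scale. The downside is that the stated detectable effect becomes less favourable than the pilot figures suggest. Whether 60 patients suffice should be left open until those SDs and target differences are stated.

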### Randomization and blinding

Participants will be screened strictly according to the diagnostic criteria, inclusion and exclusion criteria for TN formulate in this trial. The uniquely eligible participants will be numbered by using IBM SPSS Statistics 25.0 software, the relevant parameters will be entered in the syntax editor, and they will be randomly divided into EA and sham EA groups in a 1:1 ratio. Due to the particularly of the acupuncture treatment, a single-blind method will be applied in this study. Importantly, the patients, outcomes assessor, and statistician will be blinded. To ensure better implementation of the blinding method, each participant will be treated individually to minimize discussion about the acupuncture treatment methods, feelings and the therapeutic effects. We will inform the patients that due to individual difference, each person may experience the stimulation differently. At the end of the 4-week treatment period, participants will be asked to indicate whether they had received real EA or sham EA. The proportions of participants who believed they received real EA will then be compared between the two groups.

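### Thirty per group does not cover 20% dropout from the stated minimum of 25: it leaves 24 and tolerates at most 16.7%

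*Protocol article*

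**What the plan says.** All the figures are in the Sample size section of the protocol article. From pilot scores ("EA group: 3.9 (1.2); control group: 1.2 (0.8") and an independent two-sample t-test, it concludes that "a minimum of 25 participants per group will be required", with "two-sided α = 0.05, power = 0.8". It then makes the dropout allowance: "To account for a 20% dropout rate, the final sample size will be set to 30 per group", giving 60 in total. It closes with an assurance: "This ensures adequate power even with potential attrition". The formula for the dropout step is not printed. Allocation is 1:1 (Randomization and blinding section), so the same arithmetic applies to each arm.

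**The concern.** A dropout rate is a proportion of those randomised. To end with a required number, that number is divided by one minus the rate. Multiplying by one plus the rate gives a smaller figure and falls short. The step from 25 to 30 looks like the second operation. If so, the trial would end below its own stated minimum at exactly the attrition it says it has allowed for, and the closing assurance would not follow from the figures printed just before it. What is at stake is the accuracy of a sample-size statement that is likely to be carried into the results paper. The conduct of the trial is not affected.

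**Working it through.** **Inputs (all from the Sample size section).** Minimum per group 25; dropout 20%; final size 30 per group, 60 in total; two-sided α 0.05; power 0.80.

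**Step 1: reproduce the plan's figure.**
- Multiplying up: 25 × (1 + 0.20) = 30.0. This matches the stated 30 exactly.
- Dividing: 25 / (1 − 0.20) = 31.25, rounded up to 32. This does not match.

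The printed 30 is therefore consistent with 25 × 1.2. Because no formula is shown, that origin is an inference. The next step does not depend on it.

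**Step 2: apply the stated dropout to the stated size.**
- 30 × 0.20 = 6 lost, so 30 × 0.80 = 24 remain per group, against a minimum of 25.
- In total, 48 remain against 50.
- Largest dropout that still leaves 25 of 30: 1 − 25/30 = 5/30 = 16.7%.
- Size that would retain 25 at 20%: 31 × 0.80 = 24.8 (too few); 32 × 0.80 = 25.6 (enough). This means 32 per group, 64 in total.

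**Step 3: what the shortfall could cost in power.** The document states no standardised effect that yields 25 per group, so one has to be assumed. Suppose 25 per group gives exactly 80% power.

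| Method | Effect solved from n = 25 | Power at 25 | Power at 24 |
|---|---|---|---|
| Two-sample t-test (noncentral t) | d = 0.809 | 80.0% | 78.3% |
| Normal approximation | d = 0.792 | 80.0% | 78.4% |

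The loss is 1.6 to 1.7 percentage points under that assumption.

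**Step 4: does the assumption agree with the printed pilot values?** The bracketed values are not labelled; they are read here as standard deviations.
- Difference: 3.9 − 1.2 = 2.7.
- Pooled SD: √((1.2² + 0.8²)/2) = √1.04 = 1.02.
- d = 2.7/1.02 ≈ 2.65.
- Normal formula, n = 2(1.960 + 0.842)² × SD²/2.7²: 2, 3 and 4 per group for SD 0.8, 1.02 and 1.2.
- Exact t-test: 3, 4 and 5 per group for the same SDs.
- For 25 per group to follow from a difference of 2.7, the SD would have to be 2.7/0.792 ≈ 3.4.

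The assumption does not agree with them. The 25 is not reproduced from the printed inputs, and on those inputs power at 24 per group is effectively 100%. Step 2 is unaffected, because it uses only the 25, the 20% and the 30. Step 3 remains hypothetical.

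**The case against.** Four arguments can be made on the other side.

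- **The shortfall is trivial.** It is one participant per group and, even on the assumption that gives it most weight, under two points of power. This stands, and it is why the point is minor. It does not make the three printed numbers agree.
- **Dropouts stay in the analysis.** The Statistical methods section uses a modified intention-to-treat population with multiple imputation for continuous outcomes. That keeps participants in the analysis set, but it does not restore the information lost with their outcomes, and it does not make 30 the right inflation of 25. The protocol's own dropout allowance already treats attrition as reducing the usable number.
- **Power is not shown to be inadequate.** This also stands. A reader might infer that the trial is underpowered, or that it has 78% power. The documents do not support either reading. The 78.3% comes from an effect size solved backwards from 25, while the printed pilot values, read as standard deviations, imply ample power at 24. What is missed is the stated minimum; a power shortfall is shown only conditionally.
- **The formula is not printed.** It would be too strong to say as fact that the allowance was computed as 25 × 1.2. The exact match makes this likely, but the finding needs only 30 × 0.80 = 24.

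The fact that the article condenses a fuller protocol is no answer here. Nothing is missing: the 25, the 20% and the 30 are all printed, and no other section reconciles them.

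**Conclusion.** The point holds as a minor arithmetic error. By the protocol's own figures, 20% dropout from 30 per group leaves 24, one below the stated minimum of 25; 30 per group covers dropout of up to 16.7%. This rests on no assumption beyond reading the dropout rate as a proportion of those randomised. The consequence for power, about 78.3% instead of 80%, rests on the further assumption that 25 per group gives exactly 80%, which the document does not support with an effect size. The actual power cannot be judged from the printed inputs. That the 25 does not follow from the pilot values is a separate and larger question in the same section. It limits what can be said about power here, but it does not remove the mismatch between 25, 20% and 30.

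**What to change.** Keep N = 60 and correct the text of the Sample size section. Suggested wording: *Thirty participants per group retains the minimum of 25 per group with up to 16.7% dropout; 20% dropout would leave 24 per group.* Qualify the closing assurance so that it refers to dropout of up to 16.7%. Do not insert a new power figure yet. It should wait until the 25 has been re-derived from stated and labelled inputs, and the dropout step should then be redone by dividing by one minus the dropout rate. The cost is a sentence or two and a slightly less favourable dropout figure. No extra participants are needed, and randomisation, conduct and analysis do not change.
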